## Trial status

### Recruiting

Enrolment of the first patient was performed in January 2013.

## Appendix

### escription of surgical and medical treatment

After confirmed respectability of the pancreatic process, patients are randomized either to the pylorus-preserving group or the pylorus-resecting group. When the pylorus is preserved, the transsection toward the specimen is carried out 1 cm distal to the pylorus by dividing the duodenum with a linear stapling and cutting device (GIA 75 mm, blue cartridge). In the pylorus resection group, this transsection is performed 1 cm proximal to the pylorus. Consequently, the stomach is divided by a linear stapling and cutting device (GIA 75 mm, green cartridge). The pylorus remains attached to the resection specimen. The further surgical procedure of resection and lymphadenectomy is carried out similarly in both groups as usual and according to local standards regarding the indication for the intervention.

After completion of the pancreatic and the bile duct anastomosis, the gastro-enteric passage is restored by either an end-to-side duodeno-jejunostomy in a two-layer fashion, using running sutures PDS 4-0 or by an end-to-side gastro-jejunostomy for which the same technique is used (two-layer, running sutures PDS 4-0). The anastomosis is located approximately 50 cm distal of the bile duct anastomosis in an antecolic position in both groups. A gastric tube is placed in the stomach without passing the anastomosis. This tube is removed after respiratory spontanization of the patient and removal of the endotracheal tube after the operation.

The expertise of the surgeon (board certified versus no certificate) who is performing the duodenal or gastric anastomosis has to be documented.

Duration of surgery (time from skin cut until closure (minutes)) and estimated blood loss (ml) will be documented.

### Permitted and not permitted medication(s)/treatment(s)

Standard medical treatment includes prokinetic medication with metoclopramide 3 × 10 mg/day either i.v. or orally and proton pump inhibition with pantoprazole 1 × 40 mg i.v. or per os. Antibiotic treatment includes the perioperative prophylaxis with mezlocillin and metronidazole or ciprofloxacin and metronidazole in case of an intolerance of penicillin-derived drugs. Additional postoperative care is performed according to the principles and standard of the department (pain treatment, fluid resuscitation).

Nasogastric tubes are removed immediately after the operation. Reinsertion is documented in the CRF with time of reinsertion and duration of the treatment.

Octreotide analogs can be used in cases with ‘high-risk’ pancreatic anastomoses according to the department guidelines. Antibiotics can be administered if necessary.

Erythromycin must not be used as an antibiotic agent. It is administered in case of delayed gastric emptying as a prokinetic drug for a three day period. Dosage, time of application and duration of the treatment must be recorded in the CRF.

Total parenteral nutrition is allowed in case of delayed gastric emptying. Dosage, time of application and duration of the treatment must be recorded in the CRF.

The occurrence of a lymphatic fistula that requires nihil per os treatment and total parenteral nutrition is a criterion that excludes the patient from the study as this interferes with the study endpoints.

Patients should receive the medical treatment according to the clinical situation. Any protocol violation has to be reported with a clear description in the CRF.

Endoscopic examination of the duodeno-jejunostomy or gastro-jejunostomy, respectively will be performed in case of DGE after three days of conservative treatment without success. Dilation of the anastomosis can be performed in case of suspected stenosis.

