## Methods

### Study population

The study population consists of all patients scheduled for PD for any indication. Further inclusion criteria are age equal or older than 18 years and having given informed consent. Participation in another intervention trial with interference of intervention and/or outcome of this study and expected lack of compliance as well as language problems represent the only exclusion criteria. The study protocol has been approved by the local ethics committee (University of Heidelberg S-121/2012).

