### Randomization and surgical procedures

Patients are intraoperatively randomized to either of the two groups after the surgeon has confirmed that preservation of the pylorus is technically and oncologically possible. Randomization is performed as an unstratified block randomization with fixed block sizes in a 1:1 allocation ratio using established randomization software. Block size is kept confidential until completion of recruitment. Standard PD with preservation of the pylorus is performed by dividing the duodenum 2 cm distal of the pylorus with a linear stapling device under preservation of the gastric vessels along the lesser and the greater curvature. Antecolic duodeno-jejunostomy is performed at the end of the operation approximately 50 cm distal to the hepato-jejunostomy by an end-to-side anastomosis using two-layer monofilament atraumatic running sutures. Resection of the pylorus is performed with preservation of the stomach by the use of a linear stapling device with complete preservation of the gastric vessels along both curvatures to preserve perfusion of the distal stomach via the gastroepiploic arcade and the left gastric artery, respectively. Antecolic gastro-enterostomy is performed by an end-to-side gastro-jejunostomy using a two-layer running monofilament atraumatic suture technique as well. In both groups, nasogastric tubes are removed as soon as mechanical ventilation is stopped, usually at the end of the operation. Follow-up examinations are scheduled at day 7, 14 and 30 postoperatively. The study protocol is shown in Figure 
1.

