### Study objectives

Primary efficacy endpoint is the frequency of postoperative DGE according to the international ISGPS definition (Table 
1) 30 days after index operation, compared between the two intervention groups
[7]. Key secondary endpoints are operation time (skin cut to last knot), blood loss (ml), overall morbidity according to the Clavien-Dindo classification
[12], 30-day mortality, postoperative hospital stay and QoL on postoperative day 30.

**Table 1 T1:** **DGE (grading A-C) according to the ISGPS definition**[7]

**Grade**	**Nasogastric tube**	**Solid food intake**	**Vomiting distension**	**Prokinetic medication**
**A**	4-7d/reinsertion > d3	d7	±	±
**B**	8-14d/reinsertion > d7	d14	+	+
**C**	>14d/reinsertion > d14	d21	+	+

DGE, delayed gastric emptying; ISGPS, International Study Group for Pancreatic Surgery.

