#### Information bias

All surgeons who participate in this trial will be instructed which treatment procedures are applicable in both groups. Blinding of surgeons is not feasible due to the nature of the interventions. However, patient and observer documenting the endpoints during the postoperative visits will be blinded.

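### Excluding patients after randomisation for a lymphatic fistula that needs fasting and parenteral nutrition means the DGE comparison is no longer fully between the groups as randomised

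*Protocol article*

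**What the plan says.** - **Timing of allocation** (Randomization and surgical procedures): "Patients are intraoperatively randomized to either of the two groups", once the surgeon has confirmed that the pylorus can be preserved.
- **Exclusion rule** (Appendix, Permitted and not permitted medication(s)/treatment(s)): the trigger is "The occurrence of a lymphatic fistula that requires nihil per os treatment and total parenteral nutrition". The consequence given for such an event is that it "is a criterion that excludes the patient from the study as this interferes with the study endpoints". The patient leaves the study, not merely a per-protocol set.
- **Parenteral nutrition in DGE** (same section): "Total parenteral nutrition is allowed in case of delayed gastric emptying".
- **Primary endpoint** (Study objectives): "Primary efficacy endpoint is the frequency of postoperative DGE according to the international ISGPS definition", 30 days after the operation. Table 1 grades DGE by nasogastric tube use, time to solid food (day 7 in the row for grade A), vomiting or distension, and prokinetic use.
- **Exclusion list** (Study population): participation in an interfering trial, together with "expected lack of compliance as well as language problems represent the only exclusion criteria". Lymphatic fistula is not on it.
- **Analysis sets** (Documentation and data handling): the safety analysis takes every patient who received one of the interventions. The article describes no set for the primary endpoint.

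**The concern.** A lymphatic fistula, and the decision that it needs fasting and parenteral nutrition, can only arise after allocation and surgery. Removing these patients selects on the postoperative course, while the section on confounding relies on randomisation alone to keep the groups comparable.

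The selection is not clearly neutral for the endpoint. A patient fasted long enough to miss the solid-food milestone in Table 1 would tend to count as DGE, so the rule may preferentially remove events. The stated reason for the rule, interference with the endpoints, concedes the link. Because parenteral nutrition is also allowed in DGE, a patient with features of both conditions may be kept or removed according to which label is applied.

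If the frequency of exclusion differs between arms and the excluded patients have more DGE than average, the primary comparison is biased. Hospital stay, quality of life and Clavien-Dindo morbidity may lose the same patients, although the fistula is itself morbidity. A patient taken out of the study may also have no day-30 data, and an analysis set defined later could not repair that.

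**Working it through.** **1. The plan's own sample size.** Inputs from Sample size calculation: 32% versus 12%, two-sided 5%, power 90%. With pooled variance and no continuity correction, mean rate 0.22:

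n = [1.960·√(2·0.22·0.78) + 1.282·√(0.32·0.68 + 0.12·0.88)]² / 0.20² = (1.148 + 0.729)² / 0.04 ≈ 88.1, rounded up to 89 per group (power 90.3%).

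With the 10% allowance, 178/0.9 = 197.8, so 198 in total or 99 per group. Both stated figures reproduce.

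**2. Loss of numbers.** At 32% versus 12% (normal approximation), excluding 0%, 5%, 10% or 15% of 99 per group gives power of 93.1%, 91.8%, 90.3% or 88.6%. Power is not the main issue.

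**3. Bias when there is no true effect.** The documents give no fistula rate, so the excluded fractions f and the share q of excluded patients who would have had DGE are assumptions. With true rate p, the rate seen after exclusion is

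(p − f·q) / (1 − f).

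Take p = 0.32 in both arms. For f = 0.05 and q = 1: (0.32 − 0.05)/0.95 = 28.4%. For f = 0.10 and q = 1: (0.32 − 0.10)/0.90 = 24.4%. For q = 0.5 the same fractions give 0.295/0.95 = 31.1% and 0.27/0.90 = 30.0%.

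The type I error comes from exact binomial enumeration of the uncorrected chi-square test, with 99·(1 − f) patients per arm rounded to whole patients:

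| Excluded (ppPD vs prPD) | q | Observed rates | Spurious difference | Type I error |
|---|---|---|---|---|
| 5% vs 5% | 1 | 28.4% vs 28.4% | 0 | 4.9% |
| 5% vs 10% | 0.32 (average risk) | 32.0% vs 32.0% | 0 | 5.25% |
| 5% vs 10% | 0.5 | 31.1% vs 30.0% | 1.1 points | 5.4% |
| 5% vs 10% | 1 | 28.4% vs 24.4% | 4.0 points | 9.3% |
| 2% vs 4% | 1 | 30.6% vs 29.2% | 1.4 points | 5.5% |
| 2% vs 10% | 0.5 | 31.6% vs 30.0% | 1.6 points | 6.0% |
| 2% vs 10% | 1 | 30.6% vs 24.4% | 6.2 points | 15.8% |

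The 5.25% in the unbiased row reflects only the discreteness of the test, so the 5.4% below it is almost no inflation. A lower common rate is less forgiving: at p = 0.22 and q = 1, 5% versus 10% gives 17.9% versus 13.3%, a difference of 4.6 points and an error of 13.5%. Reversing the arms reverses the sign of the spurious difference.

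**4. Equal exclusion under the planned effect.** With 32% versus 12% and 5% of each arm removed, all with DGE, the observed rates are 0.27/0.95 = 28.4% and 0.07/0.95 = 7.4%. The difference is 21.1 points, against a true 20.

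**5. Cost of keeping the patients but scoring every one as DGE.** Assume 5% fistula per arm, independent of DGE. Rates become 0.32 + 0.05·0.68 = 35.4% and 0.12 + 0.05·0.88 = 16.4%. Exact power with 99 per arm is 87.5%, against 92.4% if these 5% are dropped at random with respect to DGE (94 per arm, 32% versus 12%). The scoring rule therefore matters.

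**The case against.** The other side has a fair case, and much of it limits the point.

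- **Scope.** A reader might infer that any lymphatic fistula leads to removal. Only one that requires fasting and parenteral nutrition does.
- **Who decides.** A reader might infer that unblinded surgeons apply the rule. The document says "Blinding of surgeons is not feasible due to the nature of the interventions" but not who diagnoses the fistula or excludes the patient. It also says that patients and the observers who document endpoints are blinded. That lowers the risk of unequal exclusion, though it does not restore the randomised comparison.
- **Contradiction with the exclusion list.** The list that "represent the only exclusion criteria" stands under Study population and reads as entry criteria. The appendix sentence works as a later withdrawal rule. The wording needs reconciling, but this is not proof of a conflict.
- **Safety data.** A reader might infer that these patients disappear from all other outcomes. The safety analysis keeps everyone who received an intervention, so their serious adverse events should still be compared. The question is open for hospital stay, quality of life and Clavien-Dindo morbidity.
- **Mechanism.** The appendix says that resection and lymphadenectomy are done alike in both groups, and nothing in the document shows why fistula rates should differ.
- **Size.** Errors of 9.3% and 15.8% need a two- or five-fold imbalance and every excluded patient to be a DGE case. The latter presumes a fast running past day 7, and no duration is given.
- **Unseen documents.** The full protocol or SAP may define an intention-to-treat set, and the remark on dilution through drop-outs may hint at one. Its absence from the article is no finding.

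What remains is the sentence itself. As written it takes randomised patients out of the study because of an event linked to the endpoint.

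**Conclusion.** The point holds in limited form. Following the appendix as written produces a post-randomisation exclusion, for one narrowly defined complication, that overlaps with how DGE is measured.

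The documents do not support a statement that the type I error is inflated. It stays near 5% if exclusion is equal by arm or if excluded patients have average DGE risk. With 32% DGE in both arms, 99 per arm and 5% versus 10% excluded, it runs from 5.4% (half would have had DGE) to 9.3% (all would). These exclusion fractions are assumptions, and the direction of any bias is equally unknown. The sample size is correct and unaffected. The case for change rests on an avoidable weakness in the primary comparison that is cheap to remove, not on a demonstrated error rate.

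**What to change.** Replace the exclusion sentence with text to this effect:

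1. Patients with such a fistula stay in follow-up to day 30 and in the primary analysis in their allocated group.
2. A rule fixed in advance, and applied by the blinded observers, says how DGE is scored when oral intake is withheld because of a fistula. Applying Table 1 unchanged is not enough, since it could count a therapeutic fast as DGE.
3. The number of such patients is reported per arm.
4. The analysis without these patients, and the alternative scoring (as DGE or as non-DGE), are sensitivity analyses only.
5. The wording is reconciled with the exclusion list under Study population.

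Enrolment began in January 2013, so day-30 data for any patient already excluded should be recovered where consent allows.

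No treatment changes, and the sample size stays at 198. The cost is an amended passage, a few patients whose DGE is harder to classify and, depending on the scoring rule, possibly a slight dilution of the effect. At the unfavourable end, with 5% fistula per arm all scored as DGE, power is about 87.5%.

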## Abbreviations

CRF: Case report form; DGE: Delayed gastric emptying; IPMN: Intraductal papillary mucinous neoplasia; IMBI: Institute for Medical Biometrics and Informatics; ISGPS: International Study Group for Pancreatic Surgery; PD: Partial duodeno-pancreatectomy; pp: Pylorus-preserving; pr: Pylorus-resecting; QoL: Quality of life; SOP: Standard operating procedure; RCT: Randomized controlled trial
